### Strength of the POSITIVE study design

There are several strengths of our study design. To summarize, within a multicenter design a systematic recruitment procedure with clear inclusion criteria is implemented. Randomisation is applied independent of investigators and therapists. The study is single blind and the success of blinding will be assessed a posteriori.

Reliability checks for the primary endpoint have been conducted prior to the first patient inclusion and thereafter once a year. Thus, we will be able to control for intra-rater shift over time.

Further, assessment and analysis of severe adverse events is a crucial component of the POSITIVE Study. Thus, our clinical trial will be the first which gives detailed information about the safety of CBT on persistent positive symptoms.

As an instrument for quality control and quality assurance the clinical trial will be monitored by a Coordination Centre for Clinical Trials. Manualized treatments with predefined adherence checks, regular supervision, and process-outcome analyses assure the quality of the study therapies.

Finally, the POSITIVE study provides an adequate sample size for the expected moderate treatment effect, has a predefined primary endpoint and multilevel secondary endpoints. The elaborated statistical analysis will be done by an external statistician.

### Lines of interpretation

There are two main lines of interpretation of the results of POSITIVE study.

First, according to our hypothesis, CBT might be superior to ST with regard to the reduction of positive symptoms. This result will be interpreted as an evidence for the specific efficacy of CBT. In this case it will be interesting, whether the cognitive biases (e.g. jumping to conclusions, external attribution style) have been changed and normalized in the CBT only and whether these changes can also be observed on a neural level. A significant association of the change of the cognitive biases on the one hand side and the change in positive symptoms on the other hand side would support the basic assumption of CBT approaches that the cognitive biases are factors which actually mediate the treatment effect. In addition such a result would substantially support psychological models of delusion formation [12] as it would show that psychological processes are involved not only in the development but also in the reduction of positive symptoms. However, if changes in positive symptoms are not associated with changes in biases questions will arise regarding the hypothesised mechanism of action in CBT. The health economical analysis will add an additional aspect of evaluation as it will focus on cost effectiveness and not on efficacy.

Second, CBT and ST might show no significant difference regarding reduction of positive symptoms. In this case CBT has no specific effect on positive symptoms and symptom changes are independent of the investigated psychotherapeutic treatments. As this trial does not include a "treatment as usual" (TAU) condition in order to maximise the statistical power the question will remain open, whether CBT and ST had any effect on positive symptoms. Effects of the "natural" course and effects of medication can not be identified using the present design. Even, if CBT and ST lead to comparable changes in positive symptoms it will be important to analyses changes in cognitive biases as these treatments might build on different mechanisms of action.

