On this background we aim to identify an effect size of more than .35 as significant given an anticipated drop out rate of 20%. An ES of .35 would be obtained if the PANSS Scores (Positive Syndrome) at the post treatment assessment were 12 for CBT and 14.5 for ST with a standard deviation of 7.14. An ES of less than .35 would be of limited clinical relevance.

This results in n = 130 per group for a power of 80% and a two-sided significance level of 5% (sample size calculated by nQuery 4.0, Panel MGT0). The confirmatory statistical analysis will be based on the intention-to-treat principle. Patients with missing PANSS-scores at T9 (post-treatment) will be included with the last observation carried forward (LOCF). In case of missing PANSS-scores at T9 the treatment effect will presumably be underestimated by using LOCF. To compensate for this underestimation the sample size should be adapted for drop out. Thus, we plan to include 330 patients (165 per study condition).

As assumptions about the real effect size cannot be based upon the literature we calculated different scenarios: in case of a lower effect size and/or drop out of more than 20% the statistical power will be reduced. For example, a reduced ES of 0.2 would result in a power of only 36% for the drop out of 20%. An increased drop out of 30%would reduce the power to 74% for the minimum ES of .35. On the other hand, a more favourable ES of 0.45 would increase the power to 85% for the maximum drop-out rate of 20%.

With a sample size of 330 individuals (165 each therapy group), ten assessments per patient, one primary analysis variable (therapy) and one covariable (center), the power should also be sufficient for a Mixed Model [42].

Table 3 gives an overview over the number of patients required in the different stages of the trial and the required effort for treatment and assessment. In order to successfully include 330 patients 6 study centers have been included which were committed to participate actively in this trial.

**Table 3 T3:** number of patients required in the different stages of the trial

	total	per center
required number of eligible patients (with 75% refusal)	1304	217
number of patients to be included (incl. 20% drop out)	330	55
number of patients to be analysed (ITT, LOCF)	330	55
number of patients to be analysed per protocol	260	44
treatment sessions (CBT and ST)	5530	922
number of visits	4620	770

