### Statistical Analysis

The primary endpoint for the biometrical evaluation (responsible statistician: CM) is the PANSS-Positive-Score of the Positive and Negative Syndrome Scale at the time of 9 months after inclusion. It will be analysed after completion of T9-assessments.

The statistical hypothesis for the confirmatory test of the primary endpoint is that the treatment groups are significantly different when analysed using multilevel linear mixed models with treatment and study centres as levels of analysis and adjustment for baseline values. The decision for maintaining or rejecting the null hypothesis will be made applying a two-sided test with α = 0.05. A two-sided test will be chosen as the published results about the comparison of CBT and ST are inconsistent. The observed effects will be described by use of means including the appropriate (one-sided) 95%-confidence intervals.

The confirmatory statistical evaluation of the efficacy of the CBT in this trial will be restricted to the primary endpoint. Only the rejection of the null hypothesis will be interpreted as statistical evidence for the efficacy of CBT. The confirmatory statistical analysis will be based on the intention-to-treat principle (ITT). In addition, a "per protocol" (PP) analysis will be conducted

All secondary endpoints will be compared and statistically assessed for descriptive purposes and not in a confirmatory sense. The aim of the analysis is explorative data analysis, not hypothesis testing or generation of evidence for efficacy. Because of the explorative character of this part of the analysis, no a priori statistical analysis plan exists. If adequate, secondary endpoints will be compared and statistically assessed using covariance techniques with baseline values and centers as covariates. Changes of scores over time will be modeled using linear or non-linear or nonparametric models as adequate. In addition, appropriate statistical methods of explorative data analysis including graphical methods and descriptive statistics will be used. No interim analysis and no subgroup analyses are planned.

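### The planned reading of a non-significant result, that CBT has no specific effect, does not follow from a two-sided superiority test with this precision

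*Protocol article*

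**What the plan says.** The section Lines of interpretation in the Discussion of the protocol article sets out two readings of the result. The condition for the second is: "Second, CBT and ST might show no significant difference regarding reduction of positive symptoms". The conclusion follows directly: "In this case CBT has no specific effect on positive symptoms and symptom changes are independent of the investigated psychotherapeutic treatments". The next sentence notes that there is no treatment-as-usual arm and that therefore "the question will remain open, whether CBT and ST had any effect on positive symptoms". The remaining caveats concern natural course and medication. None concerns precision.

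The Statistical Analysis section plans a superiority test only: "The decision for maintaining or rejecting the null hypothesis will be made applying a two-sided test with α = 0.05". It adds that only rejection of the null hypothesis will count as statistical evidence for efficacy, and that effects will be described by means with one-sided 95% confidence intervals.

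The Sample size calculation gives the target, "we aim to identify an effect size of more than .35 as significant given an anticipated drop out rate of 20" per cent, and says that effects below 0.35 would have limited clinical relevance. The resulting size is: "This results in n = 130 per group for a power of 80% and a two-sided significance level of 5" per cent. Enrolment is set at 165 per arm. The same section reports that "a reduced ES of 0.2 would result in a power of only 36% for the drop out of 20" per cent.

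**The concern.** The sentence turns failure to reject the null hypothesis into a statement that the effect is absent. A two-sided superiority test without an equivalence margin cannot support that. A non-significant result may come from a negligible effect or from a relevant effect that the trial missed, and only the confidence interval helps to tell these apart.

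The stated major objective is whether CBT is specifically efficacious against ST. If the result is not significant, the sentence commits the trial in advance to reporting that CBT has no specific effect, even where the interval includes a difference that the plan itself treats as relevant.

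The second half of the sentence is a lesser matter. It can be read as saying that neither therapy influenced symptoms, a question which the following sentence leaves open.

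**Working it through.** **Inputs** (Sample size calculation unless stated): target effect 0.35; means and SD "were 12 for CBT and 14.5 for ST with a standard deviation of 7.14"; two-sided α of 0.05; 80% power; 130 per arm; 165 per arm enrolled; power of 36% at an effect of 0.20. Primary endpoint section: the PANSS positive score is the mean of seven items.

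**1. Reproducing the plan's figures.** Effect size: (14.5 − 12)/7.14 = 0.350. The two-sample t calculation (noncentral t) gives 130 per arm. Power with 130 per arm is 0.803 at 0.35 and 0.362 at 0.20. The plan's 130, 80% and 36% are all confirmed.

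**2. Probability of missing a true effect** (1 − power, no baseline adjustment):

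| True effect (SD) | 130 per arm | 165 per arm, all counting fully |
|---|---|---|
| 0.35 | 1 − 0.803 = 19.7% | 1 − 0.887 = 11.3% |
| 0.20 | 1 − 0.362 = 63.8% | 1 − 0.441 = 55.9% |

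**3. What a non-significant result can still contain.** Half-width of the two-sided 95% interval in SD units: 1.96 × √(2/n).

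- 130 per arm: 1.96 × √(2/130) = 0.243
- 165 per arm: 1.96 × √(2/165) = 0.216

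An estimate just short of significance equals the half-width, so its upper limit is twice that: 0.486 or 0.432 SD. Both exceed 0.35. The upper limit falls below 0.35 only if the estimate is below 0.35 − 0.243 = 0.107 or 0.35 − 0.216 = 0.134 SD.

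**4. Baseline adjustment.** The analysis adjusts for baseline, but the baseline–outcome correlation r is not given. Adjustment multiplies the standard error by √(1 − r²). Assuming r between 0.3 and 0.6 with 130 per arm, the miss rate at 0.35 is about 16% to 6%. At r = 0.6 the factor is √(1 − 0.36) = 0.8, and the upper limits in step 3 become 0.486 × 0.8 = 0.39 and 0.432 × 0.8 = 0.35. Only at that favourable end, with all 165 per arm counting fully, would every non-significant result exclude about 0.35.

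**5. The threshold on the endpoint's scale.** The planning difference of 2.5 (12 against 14.5) is in sum-score points. On the item-mean scale it is 2.5/7 = 0.36 points, with an SD of 7.14/7 = 1.02.

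**The case against.** The sentence stands in the Discussion of a journal article, and the operative rule is in Statistical Analysis. That rule says only that rejection counts as evidence for efficacy; it does not direct a finding of no effect. The sentence changes no test, estimate or sample size. This is true and limits the weight of the point. But the sentence still announces how the confirmatory result will be read, and it goes further than the operative rule.

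The 0.20 example lies in the range that the plan calls of limited clinical relevance, and the plan reports the 36% power openly. A reader might take the 64% as the rate of missing a relevant effect. The documents do not support that: at the plan's own threshold the figure is the conventional 20%. Limited relevance is nevertheless different from no effect.

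The 20% is also towards the high end, since an analysis of all 330 patients and baseline adjustment both reduce it. In the other direction, the plan expects LOCF to underestimate the treatment effect. The problem becomes smaller but does not disappear.

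A reader might infer that the section flatly contradicts itself. That depends on what independence from the treatments means. If it means that change did not depend on which of the two therapies was given, the next sentence follows naturally. The clause is ambiguous, and it conflicts with the next sentence on one reading only.

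**Conclusion.** The concern holds as a fault of inference in the stated reading of a null result. With the plan's figures, a true effect of 0.35 would be missed in about 20% of cases (130 per arm) or about 11% (165 per arm counting fully), and less with baseline adjustment. An effect of 0.20 would be missed in 64% or 56%. Without adjustment, a non-significant result can have an interval reaching 0.49 or 0.43 SD.

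These figures assume a two-sample comparison with equal arms and a common SD. The adjusted figures rest on an assumed correlation. The fault itself does not depend on them: even with high precision, a non-significant test would at best exclude effects above a stated size.

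Two stronger readings are not supported. The document does not claim that a null result proves the absence of an effect; its sentence is categorical but makes no claim of proof. Nor does the fault touch the confirmatory test or the sample size.

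**What to change.** 1. In Lines of interpretation, replace the sentence with a rule on the two-sided 95% confidence interval of the baseline-adjusted CBT–ST difference. If the interval includes zero and its limit in favour of CBT is below the difference corresponding to 0.35 SD, a clinically relevant specific effect is excluded. If it includes both zero and that value, the result is inconclusive.
2. State that value on the scale of the primary endpoint and name the SD it rests on. With the planning SD it is 0.36 points on the item mean (2.5 points on the sum score).
3. In Statistical Analysis, change the one-sided 95% intervals to two-sided, so that they match the test and the rule can be applied.
4. Delete the clause on symptom changes being independent of the treatments, or reword it to say that no difference between the two therapies was shown.

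No data, test or sample size changes. Recruitment was completed in January 2010 and the analysis starts in November 2010, so the rule should be fixed before then. The cost is that some null results will have to be reported as inconclusive.

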## List of abbreviations used

BMBF: Bundesministerium für Bildung und Forschung (German Federal Ministry of Education and Research); CBT: Cognitive Behavioral Therapy; CDSS: Calgary Depression Rating Scale for Schizophrenia; CGI: Clinical Global Impression; CONSORT: Consolidated Standards of Reporting Trials; CTS-Psy: Cognitive Therapy Scale for Psychosis; DGPPN: Deutsche Gesellschaft für Psychiatrie, Psychotherapie und Nervenheilkunde (German Psychiatric Association); DSM-IV: Diagnostic and Statistical Manual of Mental Disorders, Forth Edition; DSMC: Data and safety monitoring committee; eCRF: electronic Case Report Form; TAU: Treatment As Usual; FSKN: Frankfurt Self-Concept Scales; IMB: Institute for Medical Biometry; IQ: Intelligence Quotient; mCBT: modified Cognitive Behavioral Therapy; MWT-B: Mehrfachwahl Wortschatz Intelligenztest (multiple choice vocabulary intelligence test); PANSS: Positive and Negative Syndrome Scale; SCID-I: Structured Clinical Interview for the DSM-IV, Axis I; ST: Supportive Therapy
